## Abstract

**Background:**

The Bernese Pain Scale for Neonates (BPSN) is a multidimensional pain assessment tool that is already widely used in clinical settings in the German speaking areas of Europe. Recent findings indicate that pain responses in preterm neonates are influenced by individual contextual factors, such as gestational age (GA), gender and the number of painful procedures experienced. Currently, the BPSN does not consider individual contextual factors. Therefore, the aim of this study is the validation of the BPSN using a large sample of neonates with different GAs. Furthermore, the influence of individual contextual factors on the variability in pain reactions across GA groups will be explored. The results will be used for a modification of the BPSN to account for individual contextual factors in future clinical pain assessment in neonates.

**Methods and design:**

This prospective multisite validation study with a repeated measures design will take place in three university hospital neonatal intensive care units (NICUs) in Switzerland (Bern, Basel and Zurich). To examine the impact of GA on pain responses and their variability, the infants will be stratified into six GA groups ranging from 24 0/7 to 42 0/7. Among preterm infants, 2–5 routine capillary heel sticks within the first 14 days of life, and among full-term infants, two heel sticks during the first days of life will be documented. For each heel stick, measurements will be video recorded for each of three phases: baseline, heel stick, and recovery. The infants’ pain responses will be rated according to the BPSN by five nurses who are blinded as to the number of each heel stick and as to the measurement phases. Individual contextual factors of interest will be extracted from patient charts.

**Discussion:**

Understanding and considering the influence of individual contextual factors on pain responses in a revised version of the BPSN will help the clinical staff to more appropriately assess pain in neonates, particularly preterm neonates hospitalized in NICUs. Pain assessment is a first step toward appropriate and efficient pain management, which itself is an important factor in later motor and cognitive development in this vulnerable patient population.

**Trial registration:**

The study is registered in the database of Clinical Trial gov. Study ID-number: NCT 02749461. Registration date: 12 April 2016.

## Background

In order to ensure their survival, premature born infants hospitalized in a neonatal intensive care unit (NICU) are subjected to many painful diagnostic and therapeutic procedures [1–3]. Although there have been efforts in recent years to quantify, and most importantly, reduce the number of procedural exposures to pain in preterm infants, procedural acute pain remains a challenge in the NICU setting [3–5]. Often, these treatment interventions take place during a crucial period in the development of the nociceptive and central nervous systems [6–8]. There is more and more alarming evidence that repeated painful stimuli at this early age may induce both structural and functional reorganization of the nervous system [7, 9–13] and result in an altered pain response [14–16]. As a consequence, the motor and cognitive development of premature infants may be impaired [9, 13, 17–22]. In premature infants requiring intensive care, the frequency of exposure to pain and systematic implementation of preventive pain measures are therefore of key importance for their later development [4, 5]. Accurate pain measurement is the first step toward effective pain management.

### Pain assessment in neonates

Clinical pain assessment in neonates, particularly those delivered preterm, is highly challenging [4, 23]. In the clinical setting, their pain responses have to be observed and assessed using behavioral and physiological indicators, which can vary across premature infants depending on their physiological and neurological development stages [23]. Behavioral indicators used as pain assessment tools include body movements, facial expressions and crying [24]. Some pain assessments also include behavior status indicators, e.g., sleep-wake state [25, 26]. Physiological responses to pain include, for instance, changes in heart rate, respiratory rate, blood pressure, oxygen saturation, vagal tone, and peripheral blood flow [25, 27]. Recently, researchers have begun to investigate more objective approaches to pain assessment, such as measurement of heart rate variability, skin conductance and cortisol as a biomarker of stress [23, 25]. To better understand and assess neonatal pain responses at cortical level, newer brain-oriented techniques, such as electroencephalography (EEG) [28, 29] and functional magnetic resonance imaging (fMRI) [30, 31], are used [11, 32–34]. However, for systematic clinical pain assessment, exclusively observable indicators need to be considered.

Because of the complex nature of pain, multidimensional pain measures that include behavioral and physiological indicators are generally assumed to be most appropriate for the clinical setting [23]. Although most infants show both types of pain response indicators, the correlation between these two indicators is often low [25, 35]. Moreover, no consistent associations between behavioral, physiological and cortical measures of pain have been detected so far [36]. In the face of inconclusive associations between different indicators of pain, the validity of existing multidimensional tools and their choices of indicators are currently being questioned, and, to date, no universally accepted gold standard exists for neonatal pain assessment [23].

More than 40 pain assessment scales for premature and full-term infants exist to date [25, 37]. The majority were designed for research purposes and are inappropriate for routine clinical procedures (e.g., because they require extended observation periods) [25, 38]. Furthermore, only a few have undergone extensive psychometric testing and are both reliable and valid [25, 39]. Of the pain assessment scales compiled for clinical application, few have been validated in premature infants and even fewer consider individual contextual factors, e.g. gestational age (GA) and health status [23, 40].

### The Bernese pain scale for neonates

The Bernese Pain Scale for Neonates (BPSN; [41]) was developed by nurses of the University Hospital of Berne primarily for clinical use. Since its development in 1996, it has been widely used for bedside pain assessment in NICUs in the German speaking areas of Europe. Several hospitals in Switzerland have fully integrated the BPSN into their daily routine.

The BPSN is a 9-item multidimensional pain assessment tool that includes behavioral and physiological indicators. The instrument consists of seven subjective (alertness, crying, consolation, skin color, facial expression, posture, and changes in respiratory rate) and two physiological (i.e. objective) (changes in heart rate and oxygen saturation) indicators. Each item is rated on a four point Likert scale (0, 1, 2, and 3). Higher scores indicate greater pain-related distress, and a total score of 11 or higher is considered to indicate pain.

In the year 2004, the BPSN was validated to differentiate between pain and non-pain status in neonates between 27 and 41 weeks of gestation [41]. The results suggested that the BPSN is a valid and reliable pain assessment instrument for assessing acute pain in term and preterm neonates. A shortcoming of this first validation study of the BPSN is the small study population of 12 infants. Furthermore, increasing evidence indicates that pain reactions of neonates are probably influenced by more than noxious stimulation alone; individual contextual factors might also impact pain reactivity [40, 42–44]. Currently, the BPSN focuses entirely on physiological and behavioral indicators.

### Individual contextual factors

Individual contextual factors encompass individual infant characteristics (e.g., GA, gender, health status, and weight), previous pain experience, or the duration of hospitalization [23, 44]. The variability in pain responses between and within premature infants as well as the low association between behavioral and physiological pain responses may be explained by the influence of individual contextual factors [35, 42, 45, 46].

Neonatal age is the most commonly examined individual contextual factor associated with neonatal pain response [44]. Premature neonates generally seem more sensitive to painful stimulation than full-term newborns. In addition to having low reflex thresholds [47, 48], newborns lack the inhibitory control that mature brain structures would exert [49]. As a result, premature neonates display diffuse responses to noxious stimuli rather than more complex affective reactions [50]. Moreover, the association between behavioral and physiological stress responses may differ depending on GA [35]. Although older GA infants displayed a positive association between the extent of behavioral pain reaction and heart rate levels, Lucas-Thompson et al. (2008) found no association between physiological and behavioral responses in the youngest GA infants. Despite the high variability in behavioral and physiologic pain responses in premature neonates, their responses are less intense [42, 45, 51, 52].

The results of several studies suggest that facial expression in response to pain increases with GA [45, 52–55]. This difference is manly influenced by the older infants’ increased facial expressiveness, which results from their more developed nervous system and facial muscles [53, 54]. In contrast, several studies have reported no significant relationship between GA and facial expression in response to pain [44, 56]. However, the consideration of reduced facial movement in response to pain in premature neonates is important. Using pain assessment scales which rely only on facial expressions may lead clinicians to the incorrect conclusion that younger premature infants do not feel or feel less pain [57]. In addition, the presence of endotracheal tubes in premature neonates impedes using facial reaction and crying as indicators of pain because endotracheal tubes are typically secured by taping them to the skin of the face [52, 54, 57]. Therefore, the consideration of other behavioral pain indicators encoded in specific body movements (e.g., hand on face), may provide further information about pain in premature infants with extremely low GA [52, 56, 58].

Several studies have examined the influence of previous pain exposure on reaction to pain, but the findings do not provide a clear answer [44]. Some studies report that infants subjected to frequent painful procedures during their hospitalization display less intense behavioral responses to heel sticks than those who have undergone fewer procedures [46, 52, 59]. The dampened pain responses in very premature neonates may be a sign of exhaustion or a state of passivity resulting from the numerous procedures they experience during their stay in a NICU [43, 60, 61]. Contrary to those findings, other studies suggest that repeated exposure to pain may lead either to increased pain response (hyperalgesia) or to pain responses without painful stimulus (allodynia) [15, 62].

Few studies have investigated the influence of other contextual factors (e.g., gender, health status) on pain reactions in neonates, and of those that have, the results are inconsistent [44]. This might be explained by methodological limitations (e.g. the comparison of different GA groups and the use of a variety of pain assessment tools) [44]. One challenge in examining the influence of contextual factors on pain response is the associations between the individual factors [44]; for example, extremely low GA infants have a longer stay in a NICU and are exposed to a higher number of painful procedures than more mature infants. Due to the fact that contextual factors can lead to underestimation or misjudgment of pain severity [54, 63–65], further research is needed to better understand the factors that influence pain responses in neonates. Relevant contextual factors should also be considered in future pain assessment.

### Study aims

The aim of this observation study is the validation of the BPSN, using a large sample of neonates spanning a full range of GAs. The validation will involve the detection of the underlying structure of the data and the examination of the concurrent validity of the BPSN with the Premature Infant Pain Profile-Revised (PIPP-R; [26]), construct validity, interrater reliability, specificity and sensitivity. Furthermore, the variability of pain reactions over time related to behavioral and physiological patterns will be analyzed and the relationship between behavioral and physiological indicators examined. In addition, the influence of contextual factors on the variability of pain reactions across GA groups will be explored. Finally, the results of this analysis will be used for modification of the BPSN, to account for individual contextual factors in future clinical pain assessment in neonates.

Based on a previous validation study of the BPSN [41], we hypothesize that the BPSN will be a valid and reliable pain assessment tool for premature and term infants. In addition, we expect that the impact of single contextual factors on infants’ pain reaction will be described and considered for future pain assessment. In particular, we anticipate finding a difference in pain reaction depending on GA. Moreover, we hypothesize that behavioral and physiological indicators will show low association across time and that this low association may be explained by the influence of individual contextual factors.

## Methods

This prospective multisite validation study focuses on psychometric testing of the BPSN and involves repeated measurement design. The study will take place in three university hospital NICUs in Switzerland (Basel, Bern and Zurich).

In total, 150 preterm and healthy-term infants hospitalized in a NICU will be included. Consecutive sampling will be used to recruit subjects and the infants will be stratified according to GA at birth (Fig. 1). Stratification is based on the assumption that premature neonates with a lower GA will show a higher variability in pain responses, due to their neurological immaturity, than will premature neonates with a higher GA and full-term infants [42]. Therefore, larger sample sizes of premature infants with GAs between 24 0/7 and 29 6/7 weeks (*n* = 102) will be included, compared to the samples of those with GAs between 30 0/7 and 42 0/7 weeks (*n* = 48).

**Fig. 1 Fig1:**
[figure not shown]
Stratification of sample according to gestational age (GA) and expected sample numbers (n) (ELGA = extremely low gestational age; LGA = low gestational age)

### Inclusion and exclusion criteria

Premature infants born between 24 0/7 and 36 6/7 weeks of gestation will be included if they are expected to undergo 2–5 routine capillary heel sticks during the first 14 days of life. Full-term infants born between 37 0/7 and 42 0/7 weeks of gestation will be included if they are expected to have at least 2 routine capillary blood samplings during their first days of life. Furthermore, signed consent is needed from the infant’s parents, who have to understand either German or French.

Infants will be excluded if they have suffered a high-grade intraventricular hemorrhage (grades III and IV), if they have a severe life-threatening malformation or suffer from any condition involving partial or total loss of sensitivity, if they have had an arterial cord pH < 7.15, if they have had surgery for any reason, or if they have a congenital malformation affecting brain circulation and/or cardiovascular system. Infants treated with continuous positive airway pressure (CPAP) or mechanical ventilation will be included if they meet the other inclusion and exclusion criteria.

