### Measures

To establish concurrent validity, neonates’ pain expression is measured by the BPSN [41] and the PIPP-R [26]. The BPSN measures 9 indicators. The two physiological indicators will be captured on an ongoing basis from the neonate’s routine continuous monitoring records (heart rate and oxygen saturation) during the video recording. The six subjective indicators (sleeping state, crying, consolation, skin color, facial expression, posture, and breathing) will be rated by five independent and blinded video raters on a 4 point Likert scale. The raters are blinded towards the phase of the video sequence they are looking at (baseline, heel stick, and recovery). The PIPP-R, which is widely used in North America for assessing acute pain in neonates, measures five indicators of which two are physiological (heart rate and oxygen saturation). The three behavioral indicators (brow bulge, eye squeeze, and naso-labial furrow) will also be assessed by the five raters. Each indicator of the PIPP-R is numerically rated on a Likert scale from 0 to 3 points, with higher ratings reflecting the rater’s impression of more intense pain responses. Additionally, the PIPP-R accounts for GA and baseline behavioral states as contextual factors. According to the instructions of the authors, these contextual factors need only be scored if there are changes in any of the behavioral or physiological items [26]. Neonates with the youngest GAs and those in quiet sleep receive the highest scores for these indicators. The PIPP-R scores will be used as a standard reference in this study.

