Based on the findings of a systematic review [44], the following individual contextual factors will be retrieved from patient charts: demographic contextual factors, including GA at birth, gender, birth weight, nationality, parity and way of delivery; the primary diagnosis and the most common comorbidities in preterm neonates, including bronchopulmonary dysplasia, necrotizing enterocolitis, respiratory distress syndrome, patent ductus arteriosus, septic events, cardiac events and respiratory events; the health status at time of birth measured by the Clinical Risk Index for Babies (CRIB; [67]). For the time of each heel stick, the following individual contextual factors will be retrieved: postnatal age; post-menstrual age (GA at birth combined with postnatal age); weight; CPAP or mechanical ventilation at the time of the heel stick procedure; medication administered (sedatives, opioids, non-opioids, steroids, caffeine, antibiotics and catecholamines) from birth and between the recorded heel stick procedures; number of previous painful (e.g., heel stick) and non-painful (e.g., diaper change) interventions from birth and between the recorded heel stick procedures (painful and non-painful interventions were defined in a previous study [68]); number of painful and non-painful procedures in the past 24 h; time since the last painful and non-painful interventions; and, finally, type of last painful and non-painful interventions. The duration of each heel stick and the number of additional sucrose doses given during the heel stick procedures will be registered while video recording.

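### Intubated infants are scored on face and cry items that the protocol says a tube impedes, in both the BPSN and its PIPP-R reference, and the validity analyses are not described by intubation status

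*Protocol article*

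**What the plan says.** The background section on individual contextual factors says that "the presence of endotracheal tubes in premature neonates impedes using facial reaction and crying as indicators of pain", and gives the reason: the tube is usually taped to the skin of the face. The eligibility section then admits ventilated infants: "Infants treated with continuous positive airway pressure (CPAP) or mechanical ventilation will be included if they meet the other inclusion and exclusion criteria".

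Under Measures, the BPSN items left to the video raters are "sleeping state, crying, consolation, skin color, facial expression, posture, and breathing) will be rated by five independent and blinded video raters". Every BPSN item runs from 0 to 3, and "a total score of 11 or higher is considered to indicate pain". For the PIPP-R, "The three behavioral indicators (brow bulge, eye squeeze, and naso-labial furrow) will also be assessed by the five raters"; the same section says "Each indicator of the PIPP-R is numerically rated on a Likert scale from 0 to 3 points" and makes the PIPP-R the reference standard. The PIPP-R also adds points for gestational age and baseline behavioural state, but only when a behavioural or physiological item changes.

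Ventilation is among the factors taken from the chart for each heel stick: "CPAP or mechanical ventilation at the time of the heel stick procedure". The Data analyses section adds contextual factors to the linear mixed models of the BPSN scores. It does not mention them for the PIPP-R correlation, the ROC analysis or the cut-off comparison. Missing-data methods are to be chosen once the amount and pattern of missingness are known. The article gives no scoring rule for a face or cry item that the rater cannot see or hear.

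**The concern.** The authors name a condition under which certain items work poorly, enrol infants in that condition, and score them on those items in both the index scale and the reference. If tape hides part of the face or a tube silences the cry, a rater confined to 0–3 may choose a low score. BPSN facial expression and the three PIPP-R facial items would then be lowered in the same sequences by the same cause. Error shared in this way is not visible when one tool is judged against the other: an infant in pain whom both tools score low counts as agreement.

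Two uses of the results are exposed. Concurrent validity, ROC and cut-off figures pooled over all infants would mix sequences where the face is readable with sequences where it may not be. If tubes are more common at low gestational age, masking would also be hard to separate from the difference in pain reaction by gestational age that the study expects. The findings are meant to feed a modified bedside scale.

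**Working it through.** The plan states no figure on this point, so the check is score arithmetic from its item counts and ranges, followed by an illustration under stated assumptions.

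**BPSN** (9 items, 0–3 each, cut-off 11)
- Maximum: 9 × 3 = 27.
- Crying and facial expression: 2 × 3 = 6 points; 6/27 = 22%.
- If both were scored 0, the attainable maximum is 27 − 6 = 21. The cut-off moves from 11/27 = 41% to 11/21 = 52% of the attainable score.

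**PIPP-R** (5 indicators, 0–3 each, 3 of them facial, no cry item)
- Indicator maximum: 5 × 3 = 15. Facial share: 9/15 = 60%, leaving 6 points from heart rate and saturation.
- If the two contextual items also run 0–3 (an assumption; the article gives no range), the share is 9/21 = 43%, leaving 12 points.

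The reference therefore depends more on the face than the BPSN does, on either count. The item content shared by the two tools that a tube can mask is the face only.

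**Exposure.** Infants of 24 0/7 to 29 6/7 weeks: 102/150 = 68% of the sample. This is not the number affected, because the article gives no intubation rate.

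**Illustration (all inputs assumed).** Pain is present in one third of sequences. Latent intensity is standard normal, raised by 1.5 in pain. Each item loads 0.7 on it and is cut at 0.3, 1.0 and 1.7 into 0–3. The two tools share the heart rate and saturation items, and contextual points are left out. In intubated sequences, face and cry items are set to 0 together with probability z. There are 200,000 sequences per setting.

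| Intubated share | z | Pooled correlation, unmasked → masked | Intubated sequences in pain with BPSN ≥ 11, unmasked → masked |
|---|---|---|---|
| 10% | 25% | 0.910 → 0.907 | 0.661 → 0.628 |
| 10% | 100% | 0.910 → 0.898 | 0.667 → 0.532 |
| 20% | 50% | 0.911 → 0.899 | 0.661 → 0.594 |
| 40% | 25% | 0.910 → 0.898 | 0.665 → 0.630 |
| 40% | 100% | 0.911 → 0.862 | 0.668 → 0.531 |

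In this model the pooled correlation hardly moves, while detection of pain in intubated sequences can fall by up to about 0.14 (0.668 − 0.531). A good pooled correlation would therefore not show that the scale works under a tube. The values depend on the assumed loadings and thresholds and do not predict the trial's results.

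**The case against.** The strongest reply is that inclusion is deliberate and partly provided for. The scale is meant for NICU use, where the Discussion calls artificial respiration frequent and presents the BPSN's range of behavioural items as an advantage for that reason. The face is filmed for at least a minute, video quality is checked, ventilation is recorded at each heel stick, and contextual factors enter the mixed models. A rating manual outside the article may already cover masked items. All of this is fair, and it rules out treating the inclusion itself as an error. It does not reach the PIPP-R correlation, ROC or cut-off comparison, and the BPSN's other behavioural items do not help the PIPP-R, whose behavioural items are all facial.

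A reader might infer several stronger things that the article does not support:
- **That masked items are scored as no pain.** No rule says so, and coding them as missing is not excluded. To impede is also less than to make unobservable: brow and eyes may stay visible.
- **That the two scores fall together and inflate agreement.** Crying is only in the BPSN, and the PIPP-R has contextual points that the BPSN lacks, although these depend on some item changing. In the illustration the pooled correlation falls slightly.
- **That CPAP and intubation are pooled in one variable.** The text lists chart data and does not specify coding. The stated problem concerns tubes, not CPAP.
- **That a weaker response at low gestational age is an artefact.** No intubation figures by gestational age are given.
- **That the main validity analysis should drop intubated sequences or use a shortened BPSN.** The first removes part of the intended population; the second leaves the cut-off of 11 undefined.

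**Conclusion.** The concern holds as a possible, unquantified measurement problem. Items that the protocol itself calls impeded under a tube carry 22% of the BPSN maximum and 60% of the PIPP-R indicator points (43% if the contextual items are counted at 0–3). Pooled correlation, ROC and cut-off results may therefore partly reflect shared facial measurement error, and this may be confounded with low gestational age. The shift of the cut-off from 41% to 52% of the attainable score is the extreme case, in which both BPSN items are scored 0 and the cut-off is unchanged. The actual size depends on the share of intubated sequences and on how raters score a masked item, and the article gives neither. The case for acting is that the planned pooled results could not show whether the problem is present.

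**What to change.** 1. Keep all infants in the main analysis. In addition, report the BPSN–PIPP-R correlation, the ROC analysis and the cut-off comparison separately for sequences with and without an endotracheal tube, using the ventilation status already collected at each heel stick.
2. Make sure that status distinguishes intubation from CPAP, if the data capture system does not do so already.
3. Before rating starts, add a not-assessable flag to the web rating tool for BPSN facial expression and crying and for the three PIPP-R facial items, and state how flagged items enter the total scores. A masked item can then be told apart from a true 0; once a score has been forced, the two cannot be separated.

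The cost is a small amount of extra rating and analysis work. The estimates by intubation status will be less precise than the pooled ones and should be reported with their uncertainty. If rating has already begun without the flag, the first two steps can still be taken.
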